### Data Handling and Security

Data collected through the Web app, including responses to weekly questionnaires, clinical measurements (cholesterol, blood pressure, weight, and self-reported smoking), and personal data (including the name, date of birth, and mobile number), will be hosted securely by the Digital Healthcare Management (DHM) in partnership with UKCloud. Upon study completion, the host will deidentify data and transfer anonymous data to Imperial College London (ICL). In addition to the data collected through the Web app, ICL will collect secondary data pertaining to prescribed medication among study participants directly from general practices. Furthermore, ICL will analyze all data and send data in aggregate form to the AHA (see Multimedia Appendix 4).

To eliminate the potential breaches of confidentiality, all necessary measures were taken to ensure the data are safe and that all data captured electronically are only transferred in an anonymized form. The DHM will act as the data host that will initialize and run the Web app. The DHM is a provider of a complete end-to-end patient health monitoring system using mobile consumer electronics and is a preferred partner of UKCloud. The DHM will use UKCloud’s infrastructure to store the data collected through the Web app. UKCloud (formerly Skyscape Cloud Services) Enterprise Compute Cloud provides a trusted, connected, and flexible cloud platform for critical enterprise apps. It is Pan-Government Accredited by the National Cyber Security Centre from UK government accreditors. In addition, it is an N3 (the trusted broadband network for NHS healthcare) aggregator that has been approved by NHS Digital to allow NHS and non-NHS organizations to host apps and data on its cloud that connect to the N3 and transmit or store Patient Identifiable Data. UKCloud manages the external firewalls that connect to the internet and other government networks. In addition, it uses trend micro for antivirus, malware, and vulnerability scanning purposes. UKCloud notifies customers of breaches to the firewall. Data stored on UKCloud are backed up daily. The data will be stored in accordance with Vivify’s BYOD (Bring Your Own Device) and Caregiver Portal requirements. VivifyHealth is a digital health platform designed to streamline remote care. Confidentiality of the data will be maintained by the DHM and ICL through password protection of the data and stored in secure servers at ICL following a transfer from the DHM. Moreover, survey data collected via Qualtrics, a survey provider available by subscription to Imperial College London, will be accessible with a password by the study team and will not contain any personal data.

### Statistical Analysis

The feasibility of administering the AHA Cholesterol CarePlan will be judged by recruitment and dropout statistics as well as by the sociodemographic and comorbidity profile of study participants in comparison with those of invited patients and all eligible patients. The participation rate will be judged as the percentage of people who consent to take part in the study out of all invited patients. General descriptive statistics will describe the sociodemographics and comorbidities of (1) consenting study participants; (2) consenting nonparticipants; and (3) all potentially eligible study patients. Invited patients will be described in terms of self-reported smartphone ownership. This will inform the likely generalizability of subsequent findings.

Compliance with the Web app will be measured using the frequency and duration of use. Patients’ weekly participation in the Web app will be automatically tracked, as well as whether they download educational videos. Compliance with the Web app will be measured using the number of weekly questionnaires attempted, the number of questions completed, and the number of educational videos downloaded. Furthermore, compliance will be described as a percentage of content accessed out of all content presented through the Web app throughout the 12-week care plan, as well as on a weekly basis.

It is anticipated that patients may be grouped into full compliers if they complete 12 weeks, good compliers if they complete 8 weeks, poor compliers if they complete 1-7 weeks, and noncompliers if they do not complete any of the weekly AHA Cholesterol CarePlan questions. Among compliers with the Web app, medication persistence and changes in diet and physical exercise will be examined throughout the 12-week Cholesterol CarePlan, and changes in the quality of life, self-reported medication adherence will be assessed at weeks 1, 12, and 24. In addition, the self-reported quality of life will be assessed using the Short-Form Health Survey [33]. The self-reported behavioral change in relation to diet and physical exercise, as well as medication persistence, will be assessed through weekly questions in the AHA Cholesterol CarePlan. Furthermore, self-reported adherence to cholesterol- lowering medication will be examined using the MARS [32].

The acceptability of the Cholesterol CarePlan will be assessed using patients’ readiness to embrace new technologies, the usability of the Web app, and patient satisfaction. Patients’ behavior in relation to readiness to adopt new technology will be examined using the 12-item TRI [30]. The Web app usability will be assessed using the 10-item SUS [31]. Furthermore, patient satisfaction with the Cholesterol CarePlan will be assessed using a questionnaire developed by the AHA.

The efficacy of the Cholesterol CarePlan will be judged by examining the Web app compliance with changes in medication adherence and clinical risk factors. Medication adherence will be collected from secondary data using the Medication Possession Ratio and Proportion of Days Covered. These measures are based on the number of days medication supplied and the quantity of medication dispensed for each filled prescription [34,35]. A difference-in-difference (DID) analysis using multiple linear regression, controlling for education, socioeconomic deprivation, ethnicity, gender, and age will be performed. Using DID, a time-series average change in medication adherence, cholesterol, smoking, blood pressure, and body mass index over 3 time-points will be compared among full compliers and partial compliers, respectively, with Web app noncompliers. Interactions in regression models will be explored using explanatory variables. In addition, subgroups analyses (by education, socioeconomic deprivation, ethnicity, gender, and age) will explore differences in medication adherence and clinical outcomes among full compliers, partial compliers, and noncompliers with the Web app. Finally, using multiple regression modeling while controlling for education, socioeconomic deprivation, ethnicity, gender and age, average changes in diet, physical exercise, and quality of life will be examined among Web app compliers.

As this is a feasibility study, the anticipated effects are neither known in terms of the prespecified compliance level with the Web app nor in terms of the expected reduction in behavioural risk factors or clinical outcomes. The feasibility study will assess possible effects in the first place. The number of invited participants from the potentially eligible population group will be monitored each week with the invitations sent out dependent upon the response rate and the achievement of this sample size. The feasibility will be evaluated through the invitations sent out and the number agreeing to participate each week. This feasibility study will inform us of the possibility of obtaining a sample of study participants among the potentially eligible population for a larger trial. For the same reason, we will not adjust *P* value thresholds for multiple testing; statistical significance will be judged using the *P*<.05 threshold.

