**Methods:**

A prospective, observational feasibility study will be conducted to demonstrate whether the Web app may be successfully taken up by patients and will be associated with improved clinical and behavioral outcomes. The study will aim to recruit 180 study participants being prescribed cholesterol-lowering medication for at least 30 days across 14 general practices in London, England. Potentially eligible patients will be invited to use the Web app on a smartphone and visit general practice for three 20-minute clinical assessments of blood pressure, height, weight, smoking, and nonfasting cholesterol over 24 weeks. The feasibility of administering the Web app will be judged by recruitment and dropout statistics and the sociodemographic and comorbidity profile of consenting study participants, consenting nonparticipants, and all potentially eligible patients. Acceptability will be assessed using patients’ readiness to embrace new technologies, the usability of the Web app, and patient satisfaction. The efficacy of the Web app will be assessed by changes in medication adherence and clinical risk factors by levels of the Web app compliance.

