### Data Collection

The sociodemographic survey containing information on comorbidities (stroke, heart disease, hypertension, familial hypercholesterolemia, kidney disease, type 2 diabetes, and dementia), age, gender, ethnicity, education, partial postcode, and smartphone ownership will be collected among study participants through the Web app. In addition, sociodemographic data (not including smartphone ownership or education) for study participants will be obtained from their medical records by general practices. Among consenting nonparticipants, the sociodemographic survey will be administered anonymously (with no possibility of further data linkage) either using a paper or a Web-based survey. All potentially eligible patients will not be asked to respond to the sociodemographic survey. Instead, anonymous sociodemographic data will be obtained from these patients’ medical records by general practices. The number of invited individuals will be recorded by the general practice staff. Medication adherence at weeks 1, 12, and 24 will be collected from secondary data.

During the baseline visit, health care professionals will set up participants to use the Web app from their work computer with the internet using a prespecified Web address on a clinician interface of the Web app. During 20-minute consultations at weeks 1, 12, and 24, a health care professional will take and input clinical measurements (blood pressure, height, weight, smoking, and nonfasting cholesterol) into the clinician interface of the Web app (see Multimedia Appendix 1).

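### Feasibility is to be judged against the profile of invited patients, but the stated data collection yields only a count of them and a self-selected survey of decliners

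*Protocol article*

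**What the plan says.** The Statistical Analysis section makes the profile comparison one of the feasibility criteria. It will look at the "sociodemographic and comorbidity profile of study participants in comparison with those of invited patients and all eligible patients". The same paragraph then lists the groups to be described: "General descriptive statistics will describe the sociodemographics and comorbidities of (1) consenting study participants; (2) consenting nonparticipants; and (3) all potentially eligible study patients". The Methods part of the abstract gives the same three: "consenting study participants, consenting nonparticipants, and all potentially eligible patients". Invited patients as a group are in neither list, although the paragraph goes on to say that they will be described by self-reported smartphone ownership. The stated purpose is to inform generalizability.

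The data behind each group are set out under Participant Enrollment and Data Collection:

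- Decliners may, if they wish, complete a sociodemographic survey on paper or by weblink. For them, "the sociodemographic survey will be administered anonymously (with no possibility of further data linkage").
- For all potentially eligible patients, "anonymous sociodemographic data will be obtained from these" patients' medical records.
- Participants answer the survey in the app. Their practices are a second source: "sociodemographic data (not including smartphone ownership or education) for study participants will be obtained from their medical records by general practices".
- For invited patients as a group, the only item stated is that practice staff record how many there were.

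**The concern.** Invited patients consist of those who join, those who decline and return the survey, and those who decline or never answer and return nothing. The plan names the whole group as a comparator but arranges to observe only the first two parts. The third part may be large, and its profile is unknown.

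If survey return depends on age, illness or deprivation, a difference between participants and survey-returning decliners may reflect who fills in surveys, not who takes up the app. Selective return can also hide a real difference. The profile is a criterion for the primary feasibility objective and is meant to inform a later randomized trial, so a distorted picture of uptake among those invited could carry forward. Because the survey is anonymous and unlinked, the gap cannot be repaired once data collection is over.

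**Working it through.** The plan gives no figure for this comparison. The target of 180 is a recruitment aim without a calculation, so there is nothing to reproduce. The check sets the sources side by side and then illustrates the possible size of the effect.

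**Sources by group (Data Collection, Participant Enrollment)**

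| Group | Survey (self-report) | Medical records |
|---|---|---|
| Participants | yes | yes, except smartphone ownership and education |
| Consenting nonparticipants | yes, returners only | no, linkage excluded |
| All potentially eligible | no | yes |
| Invited patients as a group | not collected as such | not collected as such; number only |

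That the records include comorbidities is an inference. The survey called sociodemographic contains them, the participants' record data except only two items, and Statistical Analysis plans to describe comorbidities in the eligible group.

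The table shows three things:

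1. Participants against all eligible patients can be done record to record.
2. Participants against consenting nonparticipants can be done survey to survey.
3. Participants against all invited patients has no complete source on the invited side.

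**Effect of selective survey return (assumed values)**

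Let p be the prevalence of a condition among all decliners, and r the return rate of those with the condition divided by that of those without. Prevalence among returners = p·r / (p·r + 1 − p). Take p = 0.40:

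- r = 0.5: 0.20 / (0.20 + 0.60) = 25%, a gap of −15 points
- r = 0.75: 0.30 / 0.90 = 33.3%, −6.7 points
- r = 1: 40%, no gap
- r = 1.25: 0.50 / 1.10 = 45.5%, +5.5 points
- r = 1.5: 0.60 / 1.20 = 50%, +10 points

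If participants also have 40%, these gaps are spurious. Conversely, if participants truly have 25% and decliners 40%, r = 0.5 makes returners show 25%, and a real 15-point difference disappears.

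For scale, the 95% half-width of a 40% proportion in 180 participants is 1.96 × √(0.40 × 0.60 / 180) = 7.2 points.

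**Smartphone ownership of invited patients**

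This item is self-reported only, so it is known for participants and survey returners and for nobody else. Participants all own a smartphone by eligibility (Inclusion Criteria), and decliners invited by text message answer through a weblink. The resulting figure may overstate ownership among those invited. The documents give no basis for a size.

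**Why nonparticipants should not be set against all eligible patients**

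This is the only pair without a common source. If p = 0.40 in both groups and self-report has sensitivity 0.7 to 1.0 and specificity 0.95 to 1.0 against records (assumed), survey prevalence = p·sens + (1 − p)(1 − spec). The lowest value is 0.40 × 0.7 + 0 = 28%, and the highest is 0.40 × 1.0 + 0.60 × 0.05 = 43%. The gap from source alone is −12 to +3 points.

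**The case against.** The strongest reply is that this is loose wording and not a missing group. Participants and responding decliners together are a partial profile of those invited, and the smartphone sentence seems to use the term in that sense. The article calls the decliners consenting nonparticipants throughout and says the survey is optional, so their responder status is disclosed. The analysis is descriptive, has no threshold, and claims only to inform likely generalizability.

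Part of this stands. It would be too much to say that nothing is known about invited patients. But a partial profile selected by willingness to answer is not the comparator that the feasibility sentence names, and disclosing the selection does not remove it. Nor can an analysis plan recover data that were never collected.

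A reader might also infer that the plan sets self-reported comorbidities beside record-based ones, so that differences in source will pass for differences in uptake. The documents do not support this. Participants' data are collected from both sources, so both comparisons centred on participants can be made like with like. Nonparticipants against all eligible patients is the one pair that must mix sources, and the plan does not state it as a comparison. Which participant source goes in which table column is detail that an article may leave to the full plan.

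**Conclusion.** The point holds for the comparison with invited patients. The feasibility criterion names a group for which the stated data collection gives only a count, and the group described in its place is a self-selected set of decliners. Selective return may create or hide a difference. With an assumed 40% prevalence and relative return of 0.5 to 1.5, the shift is −15 to +10 points. The true relative return is unknown, and the anonymous survey cannot reveal it. Smartphone ownership of invited patients has the same limit.

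The point does not reach the statement in the Discussion that participants can be compared with the wider eligible population: that comparison can be made on records, provided the extracts include comorbidities as inferred above. It is also not established that any difference will be misread as an effect of uptake; the text supports only that it may be. This is a cheap improvement to a descriptive criterion and not a flaw that undermines the study.

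**What to change.** 1. Have practices add an invited yes/no flag to the anonymous record extract they already supply for all potentially eligible patients. The extract stays anonymous.
2. Compare participants with invited patients and with all potentially eligible patients using record data on every side, and name these comparators consistently in the abstract and in Statistical Analysis.
3. Keep the survey for participants versus consenting nonparticipants, self-report against self-report. Label that table as survey responders only and report the return rate among decliners.
4. Do not set survey percentages for consenting nonparticipants against record percentages for all eligible patients.
5. Describe smartphone ownership as that of participants and survey responders, not of invited patients.

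The cost is one extra field, some rewording, and invitation status kept per patient instead of as a total. Opportunistic invitations would have to be logged when they are made. Education and smartphone ownership would remain survey-only, so response bias in those two items would remain.

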### Aims and Objectives

The main aim of this work is to establish whether the AHA Cholesterol CarePlan may be administered to patients as a Web app to improve cholesterol management and lifestyle among patients prescribed a cholesterol-lowering medication. The primary study objectives are to evaluate the feasibility and acceptability of the AHA Cholesterol CarePlan delivered as a Web app. The secondary objectives are to evaluate the Web app’s efficacy.

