## Methods

### Study Design

This is a prospective, observational feasibility study involving the use of a Web app on a smartphone for 24 weeks along with the collection of clinical measurements in general practice at baseline and 12 and 24 weeks after the Web app administration.

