The Web app will send out an invitation to patients’ smartphone. Patients will be asked to log in and respond to the sociodemographic survey during baseline visit and medication adherence questions during 3 clinic visits. All other questions will be completed outside clinic. The AHA Cholesterol CarePlan consists of 12 weekly components. This includes Life Simple 7 questions; 12 weekly questionnaires pertaining to diet, physical activity, and taking of medication; 12 self-reported weight and blood pressure readings; 9 educational videos; and a Patient Satisfaction Survey. This is a total of 76 multiple choice questions (46 unique questions) and 9 videos (6 unique videos). In addition, the following questionnaires will be administered through the Web app: sociodemographics, Technology Readiness Index (TRI) [30], System Usability Scale (SUS) [31], Medication Adherence Rating Scale (MARS) [32], and Short-Form Health Survey (SF-12) [33]. This is a total of 99 multiple choice questions (55 unique questions). It should take a patient 5-15 minutes to complete questions on a weekly basis. Patients will have a week to answer each week’s questions and may resume at a later time. Patients will be sent electronic reminders to complete weekly questions and book follow-up consultations (see Multimedia Appendix 2).

No equipment will be provided for self-monitoring of blood pressure and weight, and these questions will be optional. Multimedia Appendix 3 shows a timeline of quantified assessments recorded through the Web app.

Among patients who may choose not to complete the CarePlan, the questionnaires including sociodemographics, TRI, SUS, MARS, SF-12, and Patient Satisfaction will be administered through a Web-based Qualtrics survey after 12 weeks. These patients will be asked to complete sociodemographic and MARS in clinic and all other questions outside clinic. In addition, the MARS and SF-12 will be administered after 24 weeks through a Web-based Qualtrics survey. Patients will be asked to complete the MARS in clinic and the SF-12 outside clinic. Patients will have a week to complete these questions.

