Persuasive technology using convincing and effective communication is theorized to help change behavior in relation to CVD. This technology is modeled on ideas that behaviors change only when people are motivated, able and have appropriate triggers [22]. Interventions delivered through smartphones may improve medication adherence [36]. Given the high level of penetration of smartphones among people of lower socioeconomic status, there is an opportunity for health-related mobile apps to overcome traditional barriers to CVD prevention. Nonetheless, a possible limitation of using smartphones for the prevention of CVD is the existence of the digital divide with lower socioeconomic groups retaining older technologies. An important barrier to app use is privacy concerns in relation to data sharing and personal safety. Despite observed associations between app use and positive behavioral change, there is limited evidence on the sustainability of behavioral change using apps [22].

A possible methodological threat to study design may be in selection bias with more wealthy patients owning a smartphone being able to participate in the study; we will be able to assess to what extent those who take part in our study represent the wider eligible population. Another possible limitation may be the use of self-reported questionnaires. However, the use of biometric assessments and medication prescribing may cross-validate the self-reported medication compliance. As this is a feasibility study, no sample size calculations were required. Once study effects are established, the aim is to apply for further funding to design a randomized controlled trial with fully specified sample size criteria.

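### The app's efficacy is judged by comparing self-selected users with non-users, so a difference in underlying trends can reach P<.05 with no app effect; the contrast is an association and should be reported as one

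*Protocol article*

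**What the plan says.** All points are in the protocol article.

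- **Design.** Study Design: "This is a prospective, observational feasibility study involving the use of a Web app on a smartphone for 24 weeks". Data Collection has health care professionals set participants up on the app at the baseline visit. No concurrent group goes without it.
- **Objective.** Aims and Objectives: "The secondary objectives are to evaluate the Web app’s efficacy". The abstract's Objective says the same.
- **How efficacy is judged.** Statistical Analysis: "The efficacy of the Cholesterol CarePlan will be judged by examining the Web app compliance with changes in medication adherence and clinical risk factors". Average change in medication adherence, cholesterol, smoking, blood pressure and body mass index over three time-points "will be compared among full compliers and partial compliers, respectively, with Web app noncompliers". The method is DID by multiple linear regression with education, deprivation, ethnicity, gender and age as covariates.
- **How the groups arise.** Patients are classed by the number of weeks completed, and are "noncompliers if they do not complete any of the weekly AHA Cholesterol CarePlan questions". Data Collection treats non-use as the patient's decision: "Among patients who may choose not to complete the CarePlan", the questionnaires go out by a separate web survey.
- **Decision rule.** Thresholds will not be adjusted "for multiple testing; statistical significance will be judged using the" P<.05 level.
- **Next step.** Discussion: "Once study effects are established, the aim is to apply for further funding to design a randomized controlled trial". The limitations given there are selection by smartphone ownership and self-report.

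**The concern.** Compliance is behaviour observed over weeks 1 to 12, which is also when the week-12 change in each outcome builds up. The two can move together without the app doing anything. A patient who keeps up a weekly questionnaire may be one whose tablet-taking and lifestyle were going to improve anyway. A patient who stops the tablets has less reason to open a cholesterol app, so causation can run from outcome to exposure. The link is closest for medication adherence, because the weekly questionnaires that define compliance themselves ask about taking medication.

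At stake is a stated objective. Under the plan as written, a confounded association could be reported as efficacy because P<.05, and then be treated as an established effect when a randomized trial is proposed.

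**Working it through.** The article gives no effect size, SD, power or compliance-group sizes, so there is no stated figure to reproduce. The figures below are illustrative.

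**1. What DID removes.** Let a person's outcome be a stable level plus a trend plus noise. The DID contrast is (mean change in compliers) − (mean change in noncompliers). Stable level differences cancel. What remains is app effect + (compliers' underlying trend − noncompliers' underlying trend). The contrast equals the app effect only if the underlying trends are parallel.

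**2. Can parallel trends be checked?** Visits are at baseline, 12 and 24 weeks, so only one precedes app use. A pre-app trend needs at least two points, so no check is possible for cholesterol, blood pressure, smoking or body mass index. Adherence comes from prescribing data, but the article reports it at weeks 1, 12 and 24 and gives no earlier series.

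**3. Do the covariates cover it?** All five are sociodemographic. None measures motivation, comorbidity or technology readiness.

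**4. Size if trends differ.** Set the app effect to zero and let compliers change b SD (of the change score) more than noncompliers. With group sizes n1 and n0:

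P(two-sided P<.05) = Φ(b/SE − 1.96) + Φ(−b/SE − 1.96), where SE = √(1/n1 + 1/n0).

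Assumed: b, the group sizes (within the 180 planned) and a two-sided test. Worked case, 60 v 60 and b = 0.3: SE = √(2/60) = 0.183; b/SE = 1.643; Φ(−0.317) + Φ(−3.60) = 0.376.

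| b (SD) | 60 v 60 | 90 v 30 | 126 v 54 |
|---|---|---|---|
| 0 | 5.0% | 5.0% | 5.0% |
| 0.1 | 8.5% | 7.6% | 9.4% |
| 0.2 | 19.5% | 15.8% | 23.3% |
| 0.3 | 37.6% | 29.6% | 45.4% |
| 0.5 | 78.2% | 66.0% | 86.7% |

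The 126 v 54 column uses all 180 patients in one contrast, so it is the generous case. The calculation is per contrast and ignores the covariates.

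**5. Level versus trend, by simulation.** 4,000 runs, 60 v 60, app effect zero, person SD 0.7 and visit-noise SD 0.7. The SD of a single measurement and of change are then both √(0.49 + 0.49) = 0.99.

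- Compliers 0.5 units better throughout, same trend: DID rejects 5.4%; a comparison of follow-up values alone rejects 79.2%.
- Trend differing by 0.3 units: DID rejects 38.0% without a level difference and 37.3% with one.

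**6. How a given b could arise.** Suppose 35% are full compliers and 15% noncompliers (63 v 27 of 180), and a latent trait correlates r1 with compliance and r2 with change. The gap in mean compliance liability between the top 35% and bottom 15% of a normal distribution is 1.058 + 1.554 = 2.613 SD, so b = r1 × r2 × 2.613. With SE = √(1/63 + 1/27) = 0.230:

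- r1 = r2 = 0.2: b = 0.10, rejection about 7%
- 0.3 and 0.3: b = 0.24, about 18%
- 0.5 and 0.3: b = 0.39, about 40%
- 0.5 and 0.5: b = 0.65, about 81%

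These correlations are assumptions too. They show the range, not its likely centre.

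**The case against.** **The design already guards against ordinary self-selection.** A reader might infer that self-selection will show up as an effect. The documents do not support that. Selection on level is removed by DID (step 5), the models are covariate-adjusted, and with weak or moderate selection on trend most null studies stay non-significant. Steps 4 and 6 also assume the trend difference that they then measure. This stands: the supportable word is *can*. What remains is that the design cannot tell a trend difference from an app effect, whichever is present.

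**The article is already modest.** It calls the study observational, the abstract's Methods speak of association with improved outcomes, efficacy is secondary, and Statistical Analysis says that possible effects are being assessed. The feasibility and acceptability objectives are untouched. All true, but the objective and the analysis text still say efficacy, and the Discussion does not mention selection into compliance.

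**Carry-over to the trial.** A reader might infer that the DID estimate will set the trial's sample size. The article does not say so. Statistical Analysis says that the study will inform whether participants can be recruited for a larger trial, and the Discussion refers only to fully specified sample size criteria. The supportable point is the word *established*.

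**Multiplicity.** The stated main contrasts are 5 outcomes × 2 = 10. A count running through every subgroup level would be a construction, because the subgroup analyses are described only as exploring differences. The unadjusted threshold is openly declared and is a separate matter: a stricter threshold would not remove bias.

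**Conclusion.** The concern holds as a matter of what the analysis can support. The plan judges a stated objective, efficacy, by a contrast between groups formed after baseline by patients' own app use, with no non-app control. It is valid only under parallel trends, which the design cannot check for the visit-measured outcomes and the covariates do not secure. False-positive risk per contrast is about 5% if selection is on level only, and about 30% to 45% at an assumed 0.3 SD difference in trend with the group sizes tried. It is lower with weaker selection or smaller groups and higher with stronger selection. The true trend difference cannot be derived from the documents, so a spurious result is possible rather than expected.

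**What to change.** 1. **Relabel.** In the abstract's Objective, Aims and Objectives, and Statistical Analysis, describe the compliance contrasts as the association of app engagement with change, in line with the abstract's Methods, and mark them exploratory. Add to the Discussion that they depend on parallel trends between self-selected groups and are open to reverse causation. Replace the clause about effects being established before a trial.
2. **Add a whole-cohort estimate.** Report change from baseline to weeks 12 and 24 in all who attended baseline, whatever their app use, with 95% CI and SD of change. It is uncontrolled and open to secular change and regression to the mean, so present it as descriptive input to trial planning, not as evidence of efficacy.
3. **Covariates.** Add baseline comorbidity to the compliance models, taken from medical records, which Data Collection makes available for participants. Use the technology readiness or self-reported adherence scales only if measured at baseline in every compliance group. For patients who do not complete the CarePlan, Data Collection schedules the readiness scale after 12 weeks, and possibly the adherence scale too. The adherence scale also measures something close to an outcome.
4. **Reporting.** Present the compliance contrasts mainly as estimates with confidence intervals, and do not read P<.05 as showing efficacy.

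The cost is wording, one further set of covariates and a descriptive table, with no new data collection. The downside is a more modest claim.
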